## Methods and analysis

### Aim, design and setting of the study

This study concerns an exploratory cross-sectional matched-subjects observational study and will be performed in accordance with the Declaration of Helsinki guidelines, and reported in accordance with Strengthening the Reporting of Observational Studies in Epidemiology (STROBE) guidelines. All aspects of this study have been approved by the Southern Adelaide Clinical Human Research Ethics Committee (SAC HREC), Southern Adelaide Local Health Network (SALHN) (2024/HRE00253). Trial registration at the Australian and New Zealand Clinical Trials Registry was completed before commencement of participant recruitment and enrolment (Trial Registration Number: ACTRN12626000084381, date: 22–01-2026. Universal Trial Number: U1111-1332-7067).

Recruitment is planned to commence in March 2026 and is expected to continue for approximately 6 months. Laboratory analyses will be performed in batches during and after recruitment. The investigators performing the laboratory analyses are blinded to the clinical status of the patients. Participant enrolment, clinical assessments, and sample collection will be conducted in Noarlunga Hospital (Flinders Medical Centre), Adelaide. Investigators will not be blinded to group allocation (group with patients awaiting TKA or group with healthy controls). Sample analyses and data analyses will be performed in the Neuroimmunopharmacology Laboratory of Helen Mayo South Building, University of Adelaide.

The primary aim of this exploratory study is to assess whether peripheral immune response parameters (IL-1β release following TLR-2 and TLR-4 activation) differ between painful osteoarthritic knees and pain-free controls. This will be conducted through measuring peripheral immune responses (pain biomarkers, ie, IL-1β expression), quantified from both PBMCs and SFMCs following TLR-2 and TLR-4 activation using PAM3CSK4 (PAM3, a synthetic lipopeptide which functions as an agonist for TLR-2) and lipopolysaccharide (LPS, ie, endotoxin, gram-negative bacterial cell wall component which functions as an agonist for TLR-4), between patients with symptomatic knee osteoarthritis awaiting TKA and pain-free healthy controls.

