### Clinical assessment and questionnaires

The primary outcome included EC50 (concentration-response parameter: concentration which produces 50% of the maximal effect) for IL-1β release, to determine the responsiveness of PBMC and SFMC to LPS and PAM3 stimulation. Osteoarthritis severity of the painful knee will be graded by an orthopaedic surgeon based on Kellgren-Lawrence and self-assessed pain scores will be determined by the patient preoperatively for both knees using the NRS-pain scores. Additionally, preoperative mental state will be assessed by completing two Patient Reported Outcome Measures (PROM): the Hospital Anxiety and Depression Scale (HADS) questionnaire,^34^ and the Pain Catastrophizing Scale (PCS) questionnaire.^35 36^ The HADS consists of an anxiety (HADS-A) and a depression (HADS-D) subscale, each including seven items scoring 0–3, resulting in a total maximum score of 21 per subscale. Scores of 8–11 are considered borderline anxiety or depression, whereas scores>11 are considered presumable anxiety or depression.^37^ In this study, an HADS-A or HADS-D score ≥8 will be categorised as the presence of anxiety or depression, respectively.^34 38^ The PCS is a validated questionnaire consisting of 13 statements regarding feelings and thoughts during experiencing pain.^35 36^ Patients rate these statements on a 5-point Likert scale ranging from ‘not at all’ to ‘all the time’ with the total score ranging from 0 (no catastrophising) to 52 (severe catastrophising). A score of 30 or higher is considered clinically relevant catastrophising;^36 39^ as such, patients will be considered pain catastrophizing (PC) or non-PC patients.

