### Laboratory procedures

#### PainCELL sample analysis

Venous blood collected in EDTA-coated vacutainer tubes and the synovial fluid collected in sodium citrate-coated tubes/sterile containers for the painCELL test will immediately be inverted several times to prevent blood from clotting. For the PBMC and SFMC isolation success to be maximised, the blood and synovial fluid will be cooled to room temperature before the cell isolation procedures initiate (30–60 min, depending on the ambient temperature). PBMCs are isolated using Optiprep density medium (Sigma-Aldrich #D1556; Castle Hill, NSW, Australia) as directed by the manufacturer using the mixer flotation method, as previously described.^23 26 27^ Due to the expected considerably small amount of synovial fluid available from sampling, this last step using Optiprep will not be performed for the SFMCs.

Isolated PBMCs and all SFMCs are diluted to 10^6^ cells/mL in enriched Roswell Park Memorial Institute Medium (RPMI) 1640 (10% fetal bovine serum, 2 mM l-glutamine and 1% penicillin/streptomycin) and plated into 96 well plates (100 µL per well). Various concentrations of innate immune stimulants will be added into the wells which include a TLR-2 agonist (Pam3; Merck #506350; Darmstadt, Germany; from 12.5 pg/mL to 1 mg/mL), and a TLR-4 agonist (LPS; InvivoGen #TLRL-3PELPS; San Diego, California, USA; from 12.5 pg/mL to 10 mg/mL) in a final volume of 200 mL/well. Plates are then incubated for 24 hours, following which 150 mL of the supernatant will be removed, transferred to a separate 96 well plate and stored at −80°C for later analysis. Supernatants are analysed using a Human Interleukin 1 eta (IL-1β) OptEIA ELISA Set II (BD Biosciences #557953; San Jose, California, USA) per the manufacturer’s instructions. The standard curve range for this assay is estimated to be 3.9–500 pg/mL. Supernatants are added to the ELISA either neat or diluted 1:10 to ensure the quantified values fall within the limits of the standard curve.

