#### Primary outcome analysis: painCELL data

Concentration-response curves from the in vitro innate immune stimulated IL-1β release from PBMCs and SFMCs are calculated using GraphPad Prism version 8 (MathWorks; Natick, Massachusetts, USA). Differences between pain-free controls and painful symptomatic osteoarthritis patients (within the same patient for synovial fluid samples and a different patient for blood samples) will be assessed on EC_50_, Hillslope and ‘Top’ (or E_max_). The ‘Bottom’ value will be constrained to a constant of 0. An F-test in GraphPad Prism will be performed to determine if these values should be the same or different between the participant groups. The goodness of fit obtained from the TLR-2 stimulation is not sufficient to warrant presentation in the results, owing to lower-than-expected cytokine expression in the assays.

The painCELL assay cytokine data will be combined with osteoarthritis severity and NRS-pain reports, as well as other demographics (such as mental state) for each participant in a data file. Additional parameterisation of the data set will be performed to capture the delta change in cytokine release between low and high concentration innate immune challenges and between these delta values and the steepness of the concentration response.

First, a feature selection (dimensionality reduction) step will be performed to remove highly correlated variables, by examining the correlation matrix and applying the ‘Bivariate Correlations’ function to identify and exclude variables with Pearson Correlation coefficients greater than 0.8. For each specific hypothesis test, data subsets will be created using the ‘Select Cases’ function to exclude irrelevant subject data (eg, when testing the model for Healthy synovial sample Controls and the contralateral painful knee, Healthy blood sample Controls data will be excluded).

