## Ethics and dissemination

Ethical approval for this study was granted by the Southern Adelaide Clinical Human Research Ethics Committee (SAC HREC), Southern Adelaide Local Health Network (SALHN), Australia, under approval number 2024/HRE00253 (approval date 13 June 2025).

Site-level governance authorisation was subsequently obtained via Site Specific Assessment under approval number 2024/SSA00641, authorising project commencement 05 December 2025, for a period of 3 years.

All participants will provide written informed consent prior to inclusion.

No participant data have yet been generated, as participant recruitment and sample collection have not yet commenced. On completion of the study, de-identified datasets containing clinical, questionnaire and biomarker data (including peripheral immune and HS pain-signal measures analysed at the Neuroimmunopharmacology Laboratory, University of Adelaide) will be created. Because individual-level pain biomarker data may carry potential identifiability risk, the full dataset will not be made publicly available. However, de-identified data supporting the findings of the final study will be made available from the corresponding author on reasonable request, subject to approval by the SALHN governance office and compliance with ethical conditions and data-sharing regulation. Aggregated summary results will be included in the final publication, and all analytic code and statistical methods can be shared on request.

The study findings will be disseminated through publication in peer-reviewed scientific journals and presentations at national and international research conferences. Where appropriate, a plain-language summary of the study results will be made available to interested participants on request.

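### The primary outcome analysis reports a failed TLR-2 curve fit before any sample exists, contradicting the primary aim and outcome, which include TLR-2

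*Protocol article*

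**What the plan says.** All references are to the protocol article.

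- **Primary aim** (Aim, design and setting of the study): the study asks whether "peripheral immune response parameters (IL-1β release following TLR-2 and TLR-4 activation) differ between painful osteoarthritic knees and pain-free controls". The same section identifies PAM3 as the TLR-2 agonist and LPS as the TLR-4 agonist.
- **Primary outcome** (Clinical assessment and questionnaires): EC50 for IL-1β release, "to determine the responsiveness of PBMC and SFMC to LPS and PAM3 stimulation". The Sample size calculation section describes its EC50 with the same two agonists.
- **Assay plan** (PainCELL sample analysis): "Various concentrations of innate immune stimulants will be added into the wells which include a TLR-2 agonist", followed by the supplier and the concentration range for PAM3.
- **Analysis** (Primary outcome analysis: painCELL data): "The goodness of fit obtained from the TLR-2 stimulation is not sufficient to warrant presentation in the results", with the reason given as "owing to lower-than-expected cytokine expression in the assays".
- **State of the study** (Ethics and dissemination): "No participant data have yet been generated, as participant recruitment and sample collection have not yet commenced". The design section agrees: "Recruitment is planned to commence in March 2026".

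**The concern.** The sentence on TLR-2 fit is not a contingency that says what happens if the fit is poor. It reads as a finding already made, with a cause attached, in a study that has not taken a sample. It stands in the section that governs how the primary outcome is analysed, and it removes from presentation an agonist that the aim and the outcome both include.

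Two things are at stake. First, the article gives two incompatible instructions about what the primary analysis contains, so a reader of the final report could not tell whether a missing TLR-2 result follows the plan or departs from it. Second, if the sentence is followed, participants' cells are stimulated with PAM3 and the resulting EC50 comparison is left out regardless of its result. The LPS comparison would then look like the whole primary analysis. No numerical fit criterion, pilot result or citation supports the exclusion, and no corresponding statement is made about TLR-4.

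**Working it through.** **The plan's own figure.** The only calculation attached to the primary outcome is the sample size. Inputs from the Sample size calculation section: difference in EC50 2.40, within-group SD 1.78, power 90%, Type 1 error 5%. Sidedness is not stated; two-sided is assumed.

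n per group = 2 × (1.960 + 1.282)² × (1.78 / 2.40)² ≈ 2 × 10.51 × 0.550 ≈ 11.6, rounded up to 12, or 24 in total. This matches the article. A two-sample t-test calculation gives 12.6, so 13 per group, and power of 0.884 at 12 per group. Allowing for 10% loss, 12 / 0.9 = 13.3, so 14 per group; the rest of the planned 20 per group is the stated safety margin. None of this changes if TLR-2 is withheld. The point is one of consistency, not of sample size.

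**The sections side by side.**

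| Section | What it implies for TLR-2 (PAM3) |
|---|---|
| Aim, design and setting of the study | Part of the primary aim |
| Clinical assessment and questionnaires | Part of the primary outcome |
| Sample size calculation | Part of the EC50 described for sizing |
| PainCELL sample analysis | Assay will be run |
| Primary outcome analysis: painCELL data | Fit already found insufficient; not to be presented |
| Ethics and dissemination | No participant data exist |

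The first four rows cannot be held together with the fifth. The fifth and sixth cannot both be true of this study's own data. No other section supplies a pilot result or a conditional rule that would reconcile them.

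**How much is affected.** The primary outcome is EC50. Taking two cell sources (PBMC and SFMC) and two agonists (LPS and PAM3), there are 2 × 2 = 4 EC50 comparisons, of which 2 × 1 = 2 use TLR-2. The article does not state this count or assign weights to the agonists, so the safest description is one of two named agonists, in both cell sources.

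**What is not clearly affected.** The sentence concerns the concentration-response fit. The next paragraph of the same section sends painCELL cytokine data into a data file with features based on changes in cytokine release, and then to feature selection and classification. No TLR-2 exclusion is stated there, so TLR-2 values could still contribute. They would not do so as the EC50 comparison, which is the named primary outcome.

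**The case against.** The strongest reply is that this is a drafting slip. The article uses the past tense for future work elsewhere: the primary outcome is introduced with a past-tense verb, and the painHS samples are described as already frozen. The full PAM3 assay is still planned, which would be odd if the investigators had decided against TLR-2. The study is also labelled exploratory and hypothesis-generating, which limits the consequences.

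Much of this stands, and it rules out several stronger readings that a reader might infer:

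- **That the investigators have decided to suppress an unwelcome result.** The stated ground is poor fit and low cytokine expression, not the direction or significance of a difference. Nothing shows intent.
- **That the conclusion comes from an earlier study.** This is plausible, but the article names no source.
- **That no TLR-2 information could ever appear.** The classification data file may still carry it.
- **That six of twelve primary comparisons are lost.** This counts Hillslope and Top as primary outcomes. They are listed in the primary outcome analysis, but the outcome definition names EC50 alone.

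The reply does not remove the contradiction. Whatever its origin, the sentence is in the operative text for an outcome that is called primary and was used to size the study. Nor can the matter be left to a separate analysis plan: the difficulty is a positive statement in this document, not an omission from it.

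**Conclusion.** The point holds as an internal contradiction on the primary outcome, and it should be corrected before the first sample. The article states a result that the study cannot yet have. If that statement is followed, the EC50 comparisons for one of the two named agonists, in both PBMC and SFMC, go unreported whatever they show: two of four on the count above.

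This rests on two readings of the text: that the sentence refers to this study's own assays, as its place in the analysis section suggests, and that the primary outcome covers both agonists, as the aim and outcome definitions say. It does not rest on any view of motive or of the sentence's source, and the sample size is unaffected.

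**What to change.** Delete the sentence. Alternatively, replace it with one prespecified fit criterion, applied identically to both agonists and all sample types without knowledge of group, and commit to reporting the TLR-2 results and the number of failed fits by group.

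If another summary is wanted in case EC50 cannot be estimated, such as area under the concentration-response curve, compute it for all samples as a separate analysis. Substituting it for EC50 only in the samples that fail would put different quantities into one comparison.

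If TLR-2 is to be dropped on earlier evidence, cite that evidence and amend the aim, the primary outcome, the assay plan and the sample size description before the first sample. Also check that the trial registration agrees; its content was not available here.

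The cost of deletion or replacement is about a paragraph of text. The downside is that a TLR-2 table may be published that turns out to be uninformative.

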### Sample size calculation

A sample size calculation based on achieving 90% power and a Type 1 error rate of 5% was chosen. The calculation was based on primary analyses and determined that 24 participants in total (12 participants per group) would be required to detect a 2.40 difference in the Least Squares means for EC50 (concentration-response parameter: concentration which produces 50% of the maximal effect, to determine the responsiveness of PBMC and SFMC to LPS and PAM3 stimulation) assuming a within-group SD of 1.78. The clinically significant difference in EC50 was estimated based on parameters described by Evans *et al*.^29^ To account for a potential 10% loss to follow-up and safety margin with regards to sample analyses, a total sample of 40 participants (20 per group) is to be recruited.

It should be noted that the calculated sample size was based on the primary analysis and may not provide sufficient statistical power for all planned secondary analyses, such as investigating associations between immune responsiveness (PBMCs and SFMCs responses) and psychological symptoms including anxiety, depression or pain catastrophising. General statistical guidance for multivariable modelling recommends an adequate number of observations per covariate to ensure model stability (eg, 10 patients per use of 1 covariate). Therefore, the number of covariates included in secondary analyses will be kept limited (only one psychological variable per model) to maintain analytical feasibility. As these secondary analyses are exploratory in nature, their findings will be interpreted accordingly. The present study represents an initial exploratory investigation of neuroimmune pain biomarkers within an orthopaedic population.

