### Data analysis plan

Primary analyses aim to assess whether peripheral immune response parameters differ between painful osteoarthritic knees and pain-free controls. This will be evaluated using both within-subject comparisons (painful knee vs contralateral pain-free knee in patients undergoing TKA for synovial fluid analyses) and between-group comparisons (patients vs healthy controls for peripheral blood analyses). Secondary analyses will explore associations between immune response parameters and PROMs for pain intensity and psychological factors including anxiety, depression and pain catastrophising. All secondary analyses, including multivariable and machine-learning approaches, are exploratory in nature and aimed at hypothesis generation rather than confirmatory inference.

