For analysis, a randomised approach with at least a 20% holdout validation and test dataset will be employed. The dataset will be split to ensure that the test dataset is not included in the model training phase. For the categorical selection hypotheses, several classification techniques will be applied in parallel, expected to include: Linear Discriminant Analysis (LDA), Classification and Regression Trees, K-Nearest Neighbours, Support Vector Machine and Random Forest models. The best-performing model will be identified based on the highest accuracy and lowest error rate, for which a confusion matrix will then be created.

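### The random hold-out for the painCELL classifiers has no rule keeping a patient's two knees together; if knees are split, the synovial accuracy is biased downward

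*Protocol article*

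**What the plan says.** *Participants and eligibility criteria* defines the synovial data: 20 patients, each with one painful knee awaiting TKA and one pain-free contralateral knee. *Sample collection* gives the reason for aspirating the second knee, which is to reduce variability between individuals. *Data analysis plan* includes among the primary analyses "within-subject comparisons (painful knee vs contralateral pain-free knee in patients undergoing TKA for synovial fluid analyses".

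*Primary outcome analysis: painCELL data* has two layers:

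- **Curve parameters.** EC50, Hillslope and Top are compared, within the same patient for synovial fluid.
- **Classifiers.** A subset of the file is made for each hypothesis. The article's example is "when testing the model for Healthy synovial sample Controls and the contralateral painful knee". For the split, "a randomised approach with at least a 20% holdout validation and test dataset will be employed". Test data must not enter training. Linear discriminant analysis (LDA), classification trees, nearest neighbours (NN), support vector machine and random forest are then fitted, and the model with the highest accuracy is kept.

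No sentence says whether knees or patients are split, and no within-patient feature is described for the classifiers. *Data analysis plan* calls all machine-learning work exploratory.

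**The concern.** In the synovial subset the two classes are the two knees of the same people. The listed classifiers, in standard form, take each row as a separate sample. If rows are knees and are drawn at random, most held-out knees leave their partner in the training set. That partner resembles the held-out knee because it comes from the same person, but it carries the opposite label, so the model is pushed towards the wrong answer.

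Keeping test rows out of training does not prevent this. The bias runs opposite to ordinary leakage: accuracy comes out too low. In a hypothesis-generating study, that makes a synovial signal look weaker than it is.

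A second, smaller point concerns the features. Classifiers given absolute knee values keep the between-patient variation that the second aspiration was meant to remove.

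**Working it through.** **Inputs from the article.** 20 patients and 40 knees; hold-out of at least 20%, so 0.20 × 40 = 8 knees or 4 patients. The sample size is set to "detect a 2.40 difference in the Least Squares means for EC50", "assuming a within-group SD of 1.78".

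**Assumptions, not in the article.** Correlation ρ between the two knees of a patient (0 to 0.7), the number of features, and signal in one feature only.

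**Step 1: the plan's own figure.** Two independent groups, two-sided 5%, 90% power:

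n per group = 2 × (1.960 + 1.282)² × (1.78/2.40)² = 11.56, rounded up to 12, or 24 in total.

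This reproduces the stated 12 per group. The standardised effect is 2.40/1.78 = 1.35 SD. The article gives no figure for classifier accuracy.

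**Step 2: counting, with no model.** If 8 of 40 knees are drawn at random:

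- Chance that a held-out knee's partner is in training: 32/39 = 0.82.
- Expected number of such knees: 8 × 32/39 = 6.6 of 8.
- Chance that the draw is four intact pairs: C(20,4)/C(40,8) = 4,845/76,904,685, about 0.00006.

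**Step 3: effect on accuracy.** Simulation with 3 knee-level features, 3,000 runs per setting. Each cell gives the mean hold-out accuracy for the knee split / patient split.

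| ρ | True effect | 1-NN | 3-NN | LDA |
|---|---|---|---|---|
| 0 | none | 0.49 / 0.50 | 0.48 / 0.50 | 0.50 / 0.50 |
| 0.3 | none | 0.47 / 0.50 | 0.47 / 0.50 | 0.47 / 0.50 |
| 0.5 | none | 0.45 / 0.50 | 0.44 / 0.50 | 0.45 / 0.50 |
| 0.7 | none | 0.41 / 0.50 | 0.40 / 0.50 | 0.41 / 0.50 |
| 0.3 | 1.35 SD | 0.63 / 0.65 | 0.66 / 0.68 | 0.72 / 0.73 |
| 0.5 | 1.35 SD | 0.62 / 0.65 | 0.65 / 0.68 | 0.72 / 0.73 |
| 0.7 | 1.35 SD | 0.61 / 0.66 | 0.64 / 0.69 | 0.72 / 0.73 |

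Other feature counts and classifiers move these values somewhat. LDA and 5-NN at ρ = 0.5 gave 0.40-0.42 with no effect. Balancing the hold-out by label narrows the deficit to 43-46% in a four-feature run at ρ = 0.5. Over all of this, null accuracy is about 40-45% at ρ = 0.5 and about 36-47% over ρ = 0.3-0.7. The shortfall at the plan's effect is about 1-6 points.

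**Step 4: a sensitivity.** The data file also holds patient-level variables, such as mental state, that are identical for both knees. If four of these entered the synovial model at ρ = 0.5, null accuracy under a knee split would be 0.22 (1-NN), 0.29 (3-NN) and 0.33 (LDA). The patient split would still give 0.50. The article does not say that they enter this model.

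**Step 5: what a within-patient feature can add.** For one feature with 1.35 SD separation, the best single cut-off on absolute values is right with probability Φ(1.348/2) = 0.75. Choosing the painful knee from the within-patient difference is right with probability Φ(1.348/√(2(1−ρ))), which is 0.87, 0.91 and 0.96 at ρ = 0.3, 0.5 and 0.7. These are ceilings, and they answer different questions.

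**The case against.** The strongest reply is that the article never says knees are split. It speaks of the dataset, of data for each participant and of excluding subject data, and a patient-level split fits those words. Under that reading the bias is zero, as the patient-split figures show. **This stands**, and it makes the point conditional. It does not remove it. The rows of the synovial subset are knees, the article states both the split rule and its safeguard, and that safeguard does not protect paired data.

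A reader might infer that the plan discards the within-patient contrast altogether. The documents do not support that: *Data analysis plan* and *Primary outcome analysis: painCELL data* both describe a within-patient synovial comparison of the curve parameters. Only the classifiers lack a stated paired feature, so a synovial marker has another route to being seen.

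The bias at the plan's effect is also small beside the noise. One 8-knee hold-out at 70% accuracy has a standard error of √(0.7 × 0.3/8) = 0.16. **This stands too**, although noise averages to zero over repeated splits and the bias does not. Part of the null deficit is not due to pairing: at ρ = 0 a random knee split already gives 0.48-0.50 in the table, because an unbalanced draw leaves the opposite label in the majority for training.

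Finally, patient-centred values change the question. They identify which of one person's two knees hurts. The study also seeks a marker of pain in absolute terms, for which absolute values are a legitimate target. **This stands**: the centred model belongs beside the absolute-value model and should not replace it.

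**Conclusion.** The point holds in conditional form. As written, the split does not keep a patient's knees together. If knees are the unit, hold-out accuracy for the synovial hypothesis is biased downward: to about 40-45% with no true difference at ρ = 0.5, and by about 1-6 points at a 1.35 SD effect. The 82% figure needs only the 8-of-40 split. The accuracy figures rest on the assumed correlation and feature set, and would be worse if patient-level variables were used as predictors.

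Two stronger readings should be resisted. The synovial accuracy cannot be called invalid outright, because the unit of the split is unstated. Nor is the gap to a centred model (about 87-89% in simulation at the plan's effect, against 66-73% for absolute values with a patient split) accuracy that the plan loses, because the two models answer different questions.

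The bias is towards missing a signal and does not manufacture one, and the analysis is labelled exploratory. Severity is modest, but the remedy is almost free and recruitment had not begun when the article was written.

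**What to change.** In *Primary outcome analysis: painCELL data*, add to the split rule that, for the synovial hypothesis, whole patients are assigned to training or hold-out, with both knees on the same side.

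In addition, report a paired version under the same split, with each feature entered as the knee value minus the patient's two-knee mean. Place it alongside the absolute-value model and label it as showing which of a patient's two knees is painful.

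The cost is a change of wording, with no extra patients, samples or procedures. The paired version has three limits to state. It gives no absolute cut-off. Patients with only one usable synovial sample drop out of it. Its two rows per patient are mirror images, so a 4-patient hold-out carries only about 4 independent results, although it lists 8 knees.

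### The painCELL classifier plan keeps test data out of training but not out of model choice, so accuracy from as few as 8 held-out samples is likely to be optimistic and is too imprecise to interpret

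*Protocol article*

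**What the plan says.** The classifier plan is in the Protocol article under 'Primary outcome analysis: painCELL data'.

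- **Split:** "a randomised approach with at least a 20% holdout validation and test dataset will be employed". The next sentence keeps the test data out of model training. Nothing is said about keeping them out of model selection.
- **Candidates:** five methods are named (linear discriminant analysis, trees, nearest neighbours, support vector machine, random forest), as an expected list rather than a closed one.
- **Choice and report:** "The best-performing model will be identified based on the highest accuracy and lowest error rate, for which a confusion matrix will then be created". The data on which accuracy is compared are not named.
- **File contents:** the cytokine data "will be combined with osteoarthritis severity and NRS-pain reports, as well as other demographics (such as mental state) for each participant". The only stated rule for dropping variables is a pairwise correlation above 0.8.
- **Subsets:** each hypothesis uses only the relevant samples. The section's own example is painful against contralateral knees of the same patients.

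The opening of 'Data analysis plan' classes the machine-learning work as exploratory and hypothesis-generating.

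**The concern.** The article fixes the split, the candidates, the selection rule and the reported output, so this is a stated procedure and not merely detail left for later. On its natural reading, the winner's confusion matrix comes from the samples that made it the winner. The highest of several noisy accuracies overstates that model's performance on new patients, and with 8 samples the noise is large.

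Two further features of the section bear on the same accuracy. The file contains variables that largely define who is painful and who is pain-free. And in the synovial comparison the 40 samples come from 20 patients, so a random draw of single knees does not give independent training and test sets.

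At stake is whether the reported accuracy can do what the Introduction wants from the study, namely inform later work on objective pain biomarkers.

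**Working it through.** **1. The plan's own figure.** The article sizes only the EC50 comparison: "90% power and a Type 1 error rate of 5% was chosen", a "2.40 difference in the Least Squares means for EC50", "assuming a within-group SD of 1.78". Two-sided alpha is assumed.

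n per group = 2 × (1.960 + 1.282)² × (1.78/2.40)² = 11.6, so 12.

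This agrees with "24 participants in total (12 participants per group) would be required" (a t-test calculation gives 12.6, so 13). Allowing 10% loss gives 24/0.9 = 26.7, so 27; the rest of the rise to 40 belongs to the "potential 10% loss to follow-up and safety margin with regards to sample analyses". No part of this sizes a classifier.

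**2. Size of the hold-out.** Blood: 20 patients + 20 controls = 40 samples. Synovial fluid: 20 painful + 20 contralateral = 40 knees. The minimum hold-out is 0.20 × 40 = 8.

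**3. One pre-named classifier, no signal.** X ~ Binomial(8, 0.5).
- P(X ≥ 6) = (28 + 8 + 1)/256 = 14.5%
- P(X ≥ 7) = (8 + 1)/256 = 3.5%
- Expected accuracy 50%

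**4. Best of five on the same 8 samples, no signal.** If the five are independent:
- P(best ≥ 6/8) = 1 − (1 − 0.1445)⁵ = 54%
- P(best ≥ 7/8) = 1 − (1 − 0.0352)⁵ = 16%
- Expected best accuracy = (1/8) Σ over k = 0 to 7 of [1 − F(k)⁵] = 70%, with F the Binomial(8, 0.5) distribution function

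Real classifiers agree with one another. With correlated predictions (latent correlation 0.3 to 0.9, assumed), the expected best is 68% down to 60%, and P(best ≥ 6/8) is 48% down to 30%. A simulation with simplified versions of the five methods (32 training and 8 test samples, 4 per class, 6 pure-noise features, all assumed) gave 50% for each method and 65% for the best, with 75% or more in 41% of runs.

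**5. Larger or divided hold-outs.** The text says at least 20%. The expected best of five under no signal is 58–67% with 12 samples and 57–64% with 16. If 8 samples are divided 4 + 4, the choice is made on 4 and the score on the other 4 is unbiased.

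**6. Precision without selection.** Exact 95% intervals: 6/8, 35–97%; 7/8, 47–100%; 8/8, lower limit 0.025^(1/8) = 63%. With 4 test samples, even 4/4 has a lower limit of 0.025^(1/4) = 40%.

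**7. Group-defining variables.** Controls and contralateral knees are pain-free by eligibility, NRS-pain is recorded for both knees of each patient, a Kellgren-Lawrence grade is stated only for the painful knee, and healthy controls are not imaged. Adding an assumed NRS (0 in pain-free; mean 7, SD 1.5, limited to 4–10 in painful) to the noise features gave 93–100% for each method, and 100% for the best of five in every run, with no biomarker signal.

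**8. Paired knees.** If 8 of 40 knees are drawn singly, the expected number whose partner is in training is 8 × 32/39 = 6.6. Partner knees carry opposite labels, so shared patient traits pull the prediction towards the wrong class. In a no-signal simulation (20 patients, 6 features, within-patient correlation 0.5, all assumed), linear discriminant analysis and nearest neighbours averaged about 41–43%. At correlation 0.8 they averaged 25–34%. Splitting by patient gave 50%.

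**The case against.** The strongest reply has four parts.

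*Validation and test may be two sets.* This is a possible reading, and it would remove the selection bias in step 4. It does not rescue the estimate: step 6 shows that 4 to 8 test samples leave it nearly uninformative. A reader might infer that the reported accuracy will certainly be false; the documents support only that it is likely to be optimistic if one hold-out does both jobs.

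*NRS-pain and grade are in the file for other reasons.* The secondary aims relate IL-1β to pain and psychological scores, so their presence is expected, and the text nowhere says they predict group. A reader might infer that the classifier is circular as planned. That goes too far: circularity is conditional on their use, which nothing in the section rules out.

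*The pairing and the correlation filter do not inflate accuracy.* Both points stand. The unit of the split is not stated, and step 8 shows that splitting single knees pushes accuracy down under no signal. That is still distortion, and it does not arise in the blood comparison. The correlation filter screens predictors against one another without using group labels; applying it before the split made no material difference in a no-signal check (50.4% against 50.5%), so it is not counted as a cause of bias.

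*The work is exploratory.* This limits the consequence: the EC50 comparison carries the sample size, and no classification accuracy is planned as the study's main claim. The label does not correct a biased or uninformative estimate that later studies may carry forward.

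**Conclusion.** The point holds in conditional form and should be fixed. If one hold-out of 8 both selects and scores the model, the best of five averages about 60–70% when the true accuracy is 50%, depending on how strongly the classifiers agree. If validation and test are separate, the bias goes, but the result is too imprecise to interpret. Either way, the confusion matrix cannot inform a later study.

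Circularity follows only if NRS-pain or osteoarthritis grade is used to predict group. The synovial distortion follows only if knees are split singly, and under no signal it runs downward.

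These sizes assume five classifiers, the minimum hold-out and no true signal. The feature numbers, NRS distribution and correlations are assumptions that the article does not give. Because the machine learning is exploratory, this does not undermine the EC50 comparison.

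**What to change.** Replace the single hold-out with repeated nested cross-validation, or leave-one-patient-out with an inner selection loop. Specifically:

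1. Make model choice and tuning inside the training folds only.
2. Keep both knees of a patient in the same fold.
3. List the predictors for each classification question, and exclude NRS-pain, osteoarthritis grade and any other group-defining variable when group is the outcome.
4. Report outer-fold accuracy with a confidence interval and a permutation P value, labelled exploratory.

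If a hold-out is kept, say which data choose the model and which score it, and give the interval.

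The article states that no participant data exist yet, so the cost is a few sentences and a little more code. The downside is a less favourable reported accuracy. Nested cross-validation removes the selection bias and uses every sample for testing, but it does not make 40 samples precise, and the interval will remain wide.
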